## Abstract

**Background:**

Twenty to 30 percent of all transient ischaemic attacks and ischaemic strokes involve tissue supplied by the vertebrobasilar circulation. Atherosclerotic stenosis ≥ 50% in the vertebral artery accounts for vertebrobasilar stroke in at least one third of the patients. The risk of recurrent vascular events in patients with vertebral stenosis is uncertain and revascularisation of vertebral stenosis is rarely performed. Observational studies have suggested that the risk of subsequent stroke or death in patients with vertebrobasilar ischaemic events is comparable with that in patients with carotid territory events. Treatment of vertebral stenosis by percutaneous transluminal angioplasty has been introduced as an attractive treatment option. The safety and benefit of stenting of symptomatic vertebral stenosis as compared with best medical therapy alone remains to be elucidated in a randomised clinical trial.

**Study objectives:**

The primary aim of the Vertebral Artery Stenting Trial (VAST) is to assess whether stenting for symptomatic vertebral artery stenosis ≥ 50% is feasible and safe. A secondary aim is to assess the rate of new vascular events in the territory of the vertebrobasilar arteries in patients with symptomatic vertebral stenosis ≥ 50% on best medical therapy with or without stenting.

**Design:**

This is a randomised, open clinical trial, comparing best medical treatment with or without vertebral artery stenting in patients with recently symptomatic vertebral artery stenosis ≥ 50%. The trial will include a total of 180 patients with transient ischaemic attack or non-disabling ischaemic stroke attributed to vertebral artery stenosis ≥ 50%. The primary outcome is any stroke, vascular death, or non-fatal myocardial infarction within 30 days after start of treatment. Secondary outcome measures include any stroke or vascular death during follow-up and the degree of (re)stenosis after one year.

**Discussion:**

Improvements both in imaging of the vertebral artery and in endovascular techniques have created new opportunities for the treatment of symptomatic vertebral artery stenosis. This trial will assess the feasibility and safety of stenting for symptomatic vertebral artery stenosis and will provide sufficient data to inform a conclusive randomised trial testing the benefit of this treatment strategy. The VAST is supported by the Netherlands Heart Foundation (2007B045; ISRCTN29597900).

## Background

Twenty to 30 percent of all transient ischaemic attacks (TIA's) and ischaemic strokes involve tissue supplied by the vertebrobasilar (VB) circulation [1,2]. The vertebral and basilar arteries feed the brain stem, cerebellum, and thalamus, and in most people the posterior temporal and occipital lobes as well. In a large American registry of posterior circulation stroke, 22% of the patients with VB TIA or stroke had a poor functional outcome at 30 days [3]. However, some forms of VB ischaemia have a more relentless course. Occlusion of the basilar artery, for example, is associated with death or dependence in almost 80% of the cases [4].

Common causes of VB ischaemia are embolism from the heart or large arteries, or small-vessel disease [2]. In the above-mentioned registry, 32% of the ischaemic events were presumed to be caused by haemodynamic mechanisms [3]. Atherosclerotic stenosis ≥ 50% at the origin of the vertebral artery or in its intracranial course were both found in about one third of the patients.

In contrast to carotid stenosis, there has been little systematic research into the prognosis and the prevention of recurrent vascular events in patients with vertebral artery stenosis. In the carotid surgery trials, patients with ≥ 50% symptomatic carotid stenosis randomised to medical treatment alone had a 5-year risk of ipsilateral carotid ischaemic stroke of 21.2% (95% CI, 18.8 – 23.6) [5]. Similar data are not available for symptomatic vertebral artery stenosis. The best available data come from a systematic review of all published studies of prognosis after VB TIA or minor stroke, in which the risk of subsequent stroke or death in patients with VB events was similar to the risk in patients with carotid territory events [1].

In patients with carotid stenosis of 50% or greater, carotid endarterectomy (CEA) leads to an absolute reduction in the 5-year cumulative risk of ipsilateral carotid ischaemic stroke and any stroke or death within 30 days after surgery of 8.5% (95% CI, 5.6 – 11.3) [5]. Two large randomised clinical trials are currently studying carotid stenting as an alternative to CEA. Based on large case series, it is hypothesized that the trials will demonstrate the equivalence of carotid stenting as compared with CEA. By contrast, the benefit of revascularisation of vertebral stenosis is fully uncertain. Surgery to this artery is difficult due to poor access and is not considered in most centres [6]. In the last decade, treatment of vertebral stenosis by percutaneous transluminal angioplasty, usually with stent placement, has been introduced as an attractive alternative to surgery.

The endovascular access to the vertebral artery is relatively easy and the procedure can be performed without general anaesthesia, enabling continuous neurological monitoring of the patient. However, the procedure also has disadvantages. The major risk of endovascular treatment is dislodgement and distal embolisation of plaque and thrombotic debris, which may lead to stroke. In a recent review of reports on 331 endovascular treatments of vertebrobasilar stenosis, the 30-day risk of TIA, stroke, or death was 6.4% [6]. In another review of stenting procedures for vertebral or basilar artery stenosis reported up to 2005, the periprocedural risk of stroke or death was 1.6% for proximal vertebral artery stenosis and 13.8% for distal VB stenosis [7]. After a mean follow-up of one year, restenosis had occurred in one quarter of the cases of proximal vertebral artery stenting. The difference in complication rates in the treatment of proximal versus distal vertebral artery stenosis is most likely the result of several factors. First, studies of distal VB artery stenosis included lesions of the basilar artery as well. In addition, the distal procedures were much more frequently performed in the acute phase of VB artery thrombosis, and antithrombotic treatment strategies were different. For this reason, there are no reliable data on stenting of the distal vertebral artery after the acute phase.

Case series are prone to publication bias and the percentages reported above may be different in daily clinical practice. The combined 30-day incidence of any stroke or death in randomised trials on carotid stenting versus CEA, was 8.2% (126/1492) after stenting [8]. Moreover, the interpretation of outcome results after vertebral stenting is complicated by the lack of data on the risk of recurrent stroke in patients with vertebral stenosis on best medical therapy alone. Most importantly, the only trial that has compared endovascular treatment with medical therapy in a randomised fashion, included just 16 patients [6,9].

In conclusion, stenting of vertebral artery stenosis appears a promising technique for the prevention of recurrent vascular events in the VB territory, but is still without a proven benefit. The procedure may be complicated by disabling stroke and early restenosis. Before widespread application, the procedure should be assessed in a large randomised trial. As a prelude to such a trial, the present study aims to determine the safety and feasibility of stenting for symptomatic vertebral artery stenosis.

## Study objectives

The present study aims to determine whether stenting for symptomatic vertebral artery stenosis ≥ 50% in patients with a recent transient ischaemic attack or minor disabling ischaemic stroke in the posterior circulation is feasible and safe. In addition, the rate of new vascular events in the territory of the vertebrobasilar arteries will be assessed in patients with symptomatic vertebral artery stenosis ≥ 50% who receive best medical treatment or best medical treatment combined with endovascular therapy. The results will serve to design a large and conclusive randomised clinical trial in which stenting plus best medical treatment will be compared to best medical treatment alone in patients with symptomatic vertebral artery stenosis.

## Study design

This is a randomised, open, multi-centre clinical trial with masked outcome assessment, comparing the combination of vertebral artery stenting and best medical treatment with best medical treatment alone in patients with a recently symptomatic stenosis of a vertebral artery of at least 50%. A total of 180 patients will be included. Follow-up will continue until one year after inclusion of the last patient.

Endovascular treatment will be performed by an experienced interventional radiologist with a track record of at least 50 interventions in the carotid or vertebral arteries in the last 5 years. The procedure will include percutaneous transluminal angioplasty followed by stenting. The type of stent and the use of a protection device will be left to the discretion of the interventionist. If stent placement is not feasible or deemed contra-indicated, angioplasty without stent placement will be performed. The procedure will be performed under local anaesthesia, with continuous monitoring of heart rhythm and blood pressure. All patients randomised to stenting will receive clopidogrel 75 mg daily starting at least five days before the procedure and continued for 30 days after the procedure. Patients not on clopidogrel the day before the procedure should be loaded with 300 mg clopidogrel at least six hours before stenting. Best medical treatment will be left to the discretion of the neurologist, but should include rigorous control of vascular risk factors, the use of antiplatelet agents, and the use of a statin.

### Enrolment criteria

Patients can be enrolled in the study if the following criteria have been met:

1. TIA or non-disabling ischaemic stroke of the posterior circulation;

2. symptoms occurred in the 180 days preceding randomisation;

3. possibility to perform stenting within two weeks after randomisation;

4. stenosis of the vertebral artery of 50% or greater, diagnosed by both duplex ultrasound and CT angiography (CTA), contrast-enhanced MR angiography (MRA), or conventional angiography, and presumed to be of atherosclerotic origin and accessible for endovascular treatment;

5. score on the modified Rankin scale ≤ 3 (independent in daily activities, although some help may be needed) [10];

6. age 40 years or older;

7. written informed consent.

Patients will be excluded from the study in case of

1. a potential cause of TIA or minor stroke other than stenosis in a vertebral artery (e.g. atrial fibrillation);

2. a vertebral artery stenosis caused by arterial dissection;

3. previous surgical or endovascular treatment of the stenosis;

4. a life expectancy shorter than three years;

5. another serious illness that may confound outcome assessment;

6. severe renal impairment, precluding contrast administration;

7. allergy to iodinated contrast agent;

8. pregnancy.

### Posterior cerebral artery TIA or infarct

In the majority of patients, blood supply via the posterior cerebral artery (PCA) to the occipital lobes is through the VB circulation. However, in a substantial portion of patients the PCA is fully supplied by the carotid artery instead of the VB arteries [11]. For this reason, we will assess the presence of an ipsilateral P1 segment of the PCA and of an ipsilateral posterior communicating artery on the initial MRA, CTA, or conventional angiography in all patients with (transient) ischaemia in the territory of the PCA. In case of uncertainty about the supply of the PCA, direction of flow in the posterior communicating artery will be assessed, for example by means of transcranial Doppler sonography. Of the patients with ischemia in the PCA territory only, those with an exclusive supply of the PCA via the carotid artery will be excluded.

### Randomisation

A total of 180 patients will be included in the study. Patients will be randomised to either the combination of vertebral artery stenting and best medical treatment or best medical treatment alone with use of a web-based randomisation system, which includes a minimisation algorithm [12]. Randomisation will be stratified by centre and location of the stenosis (origin vs. more distal parts of the vertebral artery).

### Outcome assessment

Clinical outcome assessment will be performed by three independent adjudicators on the basis of an anonymised written description of the outcome event and ancillary investigations. This description will be made by the research physician in such a way that the adjudicators will remain masked to the allocated treatment.

The primary outcome measure will be vascular death, non-fatal myocardial infarction, or non-fatal stroke (neurological deficit lasting longer than 24 hours for which no other cause than a stroke can be found) within 30 days after start of the treatment (see Appendix for definitions).

Secondary outcome measures will be vascular death, non-fatal myocardial infarction, or non-fatal stroke during follow-up. Other outcome measures include any stroke in the supply territory of the symptomatic vertebral artery during follow-up and the degree of stenosis of the symptomatic vertebral artery after one year, as assessed with both Duplex ultrasound and CT angiography.

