### Statistical considerations

With 90 patients in the endovascular intervention arm, a complication rate of 7.8% (7 events) would yield a 95% confidence interval from 3.2 to 15.4%. The estimate of 7.8% is comparable to that of 8.2% for carotid stenting [8]. As the number of patients receiving angioplasty without stent placement is expected to be extremely small, these patients will be analysed together with the patients who have received a stent.

Inclusion of a total of 90 patients in the medical arm during three years and one final year of follow up for these patients will provide 225 patient years of follow up. This number of patient years would yield a 95% confidence interval of 4.1 to 11.5% for an annual event rate of 7%.

An additional analysis will be done to compare the incidence of vascular events between the two treatment groups. This analysis will be based on the intention-to-treat principle and reported in terms of the hazard ratio with corresponding 95% confidence intervals calculated with the Cox proportional hazard model.

We consider the precision of the above estimates sufficient for reliable calculation of the sample size of a conclusive randomised clinical trial.

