### Ethical considerations

The study will be conducted according to the principles of the Declaration of Helsinki, as amended in 2000 and clarified in 2004, and in accordance with the Dutch Medical Research Involving Human Subjects Act (WMO). Approval by the local medical ethical review board is required for each participating centre before start of patient inclusion. The patients will be informed about the trial by their treating physician but will whenever possible be asked for consent by a physician not involved in their treatment. Patients should reach a decision about participation within 180 days after the last vertebrobasilar symptom.

The trial compares two existing forms of treatment currently used in many hospitals worldwide. The investigators anticipate that some patients may be harmed inadvertently as a result of either the stenting procedure or the decision to refrain from invasive treatment. The determination of the rate of these adverse outcome events is in fact the major aim of the trial. In the majority of patients with a recently symptomatic carotid stenosis of 50% or greater, CEA reduces the long-term risk of stroke despite the risks of the intervention [5,14] but at present it is unknown whether this also applies to stenting of vertebral artery stenosis. The trial protocol does not subject patients to hazards that would not have been encountered if they had received the trial treatments outside the context of the trial in routine clinical practice, except for the very small chance of a complication of CTA performed one year after start of treatment, such as an allergic reaction or contrast nephropathy. Individual investigators and hospitals are required to take responsibility for the occurrence of any adverse events in the same way as they would do if the treatments were performed outside the trial.

The sponsor/investigator has a liability insurance which is in accordance with article 7, subsection 6 of the WMO.

The sponsor (also) has an insurance which is in accordance with the legal requirements in the Netherlands (Article 7 WMO and the Measure regarding Compulsory Insurance for Clinical Research in Humans of 23 June 2003). This insurance provides coverage for damage to research subjects through injury or death caused by the study.

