## Appendix. definitions of vascular complications

1. Death from vascular causes:

a. Fatal cerebral infarction: cerebral infarction causing an increase of handicap to Rankin 4 or 5, followed by death. Death should have been an unlikely event without the preceding infarction.

b. Fatal cerebral hemorrhage: cerebral haemorrhage causing an increase of handicap to Rankin 4 or 5, followed by death. Death should have been an unlikely event without the preceding bleeding.

c. Fatal myocardial infarction: Documented myocardial infarction (see 6) followed by death, at least one hour after onset of symptoms.

d. Definite sudden death: witnessed sudden death with reliable observation of timing; i.e. patient died within one hour after onset of symptoms.

e. Probable sudden death: witnessed death, but unreliable data on timing of events, or found dead and previously "healthy."

f. Terminal heart failure.

g. Fatal arterial bleeding.

h. Other fatal vascular complication, e.g. gastric bleeding, pulmonary embolism.

2. Cerebral infarction.

a. Definite new cerebral infarction: clinical evidence of the sudden onset of a new neurological deficit, persisting for more than 24 hours, with a corresponding new infarct on a repeat CT scan.

b. Probable new cerebral infarction: clinical evidence of the sudden onset of a new neurological deficit, or an increase in an existing deficit, persisting for more than 24 hours, without a new infarct on repeat CT scan.

3. Intracerebral haemorrhage

a. Clinical evidence of a sudden new neurological deficit, or an increase in an existing deficit, persisting for more than 24 hours, with a corresponding cerebral haemorrhage on a CT or MRI scan.

4. Subarachnoid haemorrhage

a. A sudden unusual headache and/or a reduction in consciousness with a corresponding subarachnoid haemorrhage on CT or MRI, or signs of subarachnoid haemorrhage in the cerebrospinal fluid.

5. Unspecified stroke

a. Clinical evidence of a sudden new neurological deficit, or an increase in an existing deficit, persisting for more than 24 hours, with no imaging performed.

6. Myocardial infarction

a. Myocardial infarction: At least two of the following characteristics have to be documented: a history of chest discomfort for at least half an hour, specific cardiac enzymes more than twice the upper limit of normal, or the development of specific abnormalities (e.g. Q waves) on the standard 12-lead electrocardiogram.

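### The 30-day primary safety outcome leaves out non-vascular procedure-related deaths, and its components differ from those of the 8.2% benchmark

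*Protocol article*

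**What the plan says.** The Background gives the purpose: "the present study aims to determine the safety and feasibility of stenting for symptomatic vertebral artery stenosis". The Abstract (Design) and Outcome assessment define the primary outcome consistently. The first reads "The primary outcome is any stroke, vascular death, or non-fatal myocardial infarction within 30 days after start of treatment"; the second reads "The primary outcome measure will be vascular death, non-fatal myocardial infarction, or non-fatal stroke", within the same 30 days, and refers to the Appendix for definitions.

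Appendix item 1 lists the deaths that count as vascular: fatal cerebral infarction, fatal cerebral haemorrhage, fatal myocardial infarction, definite sudden death, probable sudden death, terminal heart failure, fatal arterial bleeding, and a residual item, "Other fatal vascular complication, e.g. gastric bleeding, pulmonary embolism". Probable sudden death (item 1e) is "witnessed death, but unreliable data on timing of events, or found dead and previously" healthy, a word the protocol itself puts in quotation marks.

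Statistical considerations states that with 90 stented patients "a complication rate of 7.8% (7 events) would yield a 95% confidence interval from 3.2 to 15.4" percent, and calls the 7.8% comparable to 8.2% for carotid stenting. Safety and indemnity describes that 8.2% as the 30-day incidence of any stroke or death. Adverse event reporting proposes the same 8.2% as a stopping criterion, to be compared with the lower 95% limit of the complication rate. That section also makes every death a serious adverse event and requires a safety report for those within 30 days.

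**The concern.** In the month after a procedure, nearly any death bears on whether the procedure is safe. Appendix item 1 has no entry for a death from infection, renal failure, a contrast reaction or a procedural cause as such. The residual item is open-ended but limited to vascular complications. A death of this kind enters the primary rate only if the adjudicators stretch that item.

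Two features make this worth correcting. First, a non-vascular death caused by the procedure can occur only in patients who undergo it, so the exclusion falls on the arm whose safety is being measured. Second, the rate depends on cause-of-death classification by adjudicators who work from a description written to keep them masked to treatment. A description that conceals the procedure makes a procedural cause hard to recognise. Counting every death removes that dependence.

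The protocol also reads its rate against an outcome with different components, and proposes a stopping criterion from it.

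**Working it through.** **1. The plan's own figure.** Inputs from Statistical considerations: n = 90, x = 7. The exact (Clopper-Pearson) limits are the 0.025 quantile of Beta(x, n − x + 1) and the 0.975 quantile of Beta(x + 1, n − x). For 7/90 = 7.8% they are 3.18% and 15.37%, which reproduces the stated 3.2 to 15.4. The figure is correct.

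**2. Effect of an omitted death.** One death is 1/90 = 1.1 percentage points.

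| Events | Rate | Exact 95% CI |
|---|---|---|
| 7/90 | 7.8% | 3.2 to 15.4 |
| 8/90 | 8.9% | 3.9 to 16.8 |
| 9/90 | 10.0% | 4.7 to 18.1 |

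**3. How many such deaths.** The documents give no non-vascular death rate. The Discussion gives total mortality of 0.3% for extracranial stenting, which is 90 × 0.003 = 0.27 deaths from all causes. For distal stenting it gives 3.2%, or 90 × 0.032 = 2.88 deaths, but it notes that distal procedures were more often done in the acute phase. Non-vascular deaths can be only a part of either figure.

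For an assumed 30-day non-vascular death rate d, the chance of at least one in 90 is 1 − (1 − d)^90:

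- d = 0.3%: 24%
- d = 1%: 60%
- d = 2%: 84%

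These values of d are illustrations. The first would require the whole extracranial mortality to be non-vascular.

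**4. Components side by side.**

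| Rate | Stroke | Death | Non-fatal MI | TIA |
|---|---|---|---|---|
| Trial primary outcome | yes | vascular only | yes | no |
| Carotid stenting, 8.2% | yes | unrestricted | no | no |
| Vertebral or basilar stenting, 1.6% proximal and 13.8% distal | yes | unrestricted | no | no |
| Endovascular vertebrobasilar series ("the 30-day risk of TIA, stroke, or death was 6.4" percent) | yes | unrestricted | no | yes |

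Against 8.2%, the trial outcome loses non-vascular death and gains non-fatal myocardial infarction. The two differences work in opposite directions, and the documents size neither.

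**5. Stopping criterion.** With n = 90, the exact lower limit first exceeds 8.2% at 14 events (15.6%, lower limit 8.8%). If the counted rate were truly 15%, the chance of 14 or more events is 49%. Adding 1.1 points to that rate makes it 60%. So one death per 90 can matter near the boundary, if the complication rate means the primary outcome. The protocol does not say expressly that it does.

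**The case against.** The case for leaving the definition alone is reasonable. Vascular death is stated consistently, defined in an appendix, adjudicated under masking and carried into the follow-up composite. The main hazard that the protocol names, distal embolisation leading to stroke, is fully counted. Nothing is contradictory or miscalculated. Recruitment began on 1 June 2008, so a change would alter the primary outcome of a running trial. All of this stands, and it limits the point to an improvement in the outcome definition.

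Four stronger readings are tempting, and the documents do not support them.

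- **Contrast harms.** A reader might infer that the protocol itself names contrast harms as procedural risks. Ethical considerations does mention complications "such as an allergic reaction or contrast nephropathy", but only for the CT angiogram one year after start of treatment, outside the 30-day window. Known contrast allergy and severe renal impairment are also exclusions. A contrast death after stenting remains possible, but it is an illustration, not a risk the protocol describes.
- **Unexplained deaths.** A reader might infer that these drop out. Item 1e counts most of them. Reading its word healthy to exclude anyone with a TIA or stroke would make the found-dead clause unusable in this trial. Items 1g and 1h take in bleeding and embolic deaths.
- **Direction of bias.** A reader might infer that the primary rate is biased downwards against the cited series. Omitting deaths can only lower the trial's own rate, but the added myocardial infarction prevents any statement about direction against 8.2%, 1.6% or 13.8%, and TIA further separates the 6.4% series.
- **Lost deaths.** They are not lost. Safety reports, procedural complications recorded at visits and the monitoring committee's continuing unblinded analyses all capture them. They are missing only from the headline rate.

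**Conclusion.** The point holds as a modest and inexpensive improvement. The 30-day primary rate excludes procedure-related deaths from non-vascular causes, although procedural safety is what the trial sets out to measure. Each such death would add 1.1 percentage points. The number expected is small and cannot be fixed from the documents, and zero is quite plausible for extracranial lesions. Even one would move the interval only from 3.2–15.4 to 3.9–16.8.

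The 8.2% figure counts a different set of events, so calling 7.8% comparable to it is loose, and the sign of the discrepancy is unknown. Any consequence for the stopping criterion rests on the assumption that the complication rate is the primary outcome rate. The reproduced confidence interval is not in question.

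**What to change.** Preferred: in the Abstract (Design) and Outcome assessment, define the 30-day outcome as any stroke, non-fatal myocardial infarction or death from any cause. Give the vascular-death version of the 30-day rate as a supportive line. Keep vascular death in the follow-up composite, where it is a reasonable component.

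Alternative, if the primary definition is kept because recruitment has begun: report 30-day any stroke or all-cause death in each arm and use that rate for the 8.2% comparison. This version matches the benchmark's components as the protocol words them. The preferred outcome, which keeps myocardial infarction, still would not match, so this line is useful for the benchmark in either case.

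Under both options, state in Statistical considerations and Adverse event reporting which events make up the complication rate.

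Cost: no new data, since deaths within 30 days already require a safety report. The preferred option needs an amendment to the primary outcome of a running trial; the alternative adds only a reported line. The downside is that an occasional unrelated death is counted, about equally in both arms, so the rate may look slightly less favourable.
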